#### *Rationale for eFET*

With the development of technique for embryo freezing, especially the widespread use of vitrification, the implantation rate after frozen embryo transfer has been increasing. Data from SART in 2013 showed the implantation rate after frozen embryo transfer was similar for women under 38 years and higher in women over 38 years than that after fresh embryo transfer. Meanwhile, the supraphysiological levels of steroid hormones during fresh transfer are suspected to effect the endometrial receptivity and the implanting embryo. Observational studies showed that singleton pregnancy derived from frozen embryo transfer had lower risk of pregnancy complications than that from fresh embryo transfer. We conducted a multicenter randomized controlled trial in women with PCOS comparing elective frozen embryo transfer with fresh embryo transfer. Our results showed that frozen embryo transfer resulted in a higher rate of live birth and lower rate of pregnancy loss than fresh embryo transfer as well as a higher birth weight after frozen embryo transfer. The complications of pregnancy including twin and singleton were comparable except for a higher risk of pre-eclampsia after frozen embryo transfer versus fresh embryo transfer. This study highlights the need to capture all perinatal complications to fully inform risk-benefit counseling of patients about IVF procedures. Another recent study presented at ASRM this year of fresh vs frozen transfer in patients with unexplained infertility showed comparable ongoing pregnancy rates after fresh or frozen transfer. Thus we believe the current data are favorable supporting elective freezing of embryos having a good prognosis for ongoing pregnancy and/or live birth. At present, for women undergo PGS cycle, embryos are routinely vitrified after biopsy and frozen embryo transfer is performed if euploid embryos are obtained. To keep the two groups in our study comparable and to eliminate the confounder of fresh vs frozen transfer, subjects in the non-PGS control group will also undergo elective frozen embryo transfer.

#### *Rationale for morphologic scoring on embryos*

Embryo morphologic assessment is the most commonly used method for embryo selection in the clinical routine. The three-part scoring system for blastocysts was developed in 1999 based on blastocyst expansion, inner cell mass (ICM), and trophoctoderm (TE) development. Using this scoring system it was revealed that there was a strong correlation between the clinical outcomes (implantation rates, pregnancy)

03/07/2017

and the morphological grade of blastocysts, and the transfer of top-scoring blastocysts produces increased implantation and pregnancy rates.

Although this type of selection is simple and direct, there are also many limitations. The main limitation is that it is a static system and can be operator-dependent. More importantly, it is unable to validly reflect the chromosomal status of the embryos. Although there seems to be a relationship between the ploidy status and blastocyst morphology, the euploid embryo rate was only 40% -56% in the top-scoring blastocysts, and miscarriage rate wasn't effectively improved after the transfer of top-quality ones. Thus, morphologic evaluation alone cannot meet the growing demands for embryo selection, especially in the context of SET.

#### *Rationale for transferring mosaics: Insufficient Data at Present*

It has been reported that the majority of human pre-implantation embryos after IVF display chromosome mosaicism, of which the diploid-aneuploid mosaicism is the most common chromosomal constitution. Chromosome mosaicism is most frequently observed in embryos at the early cleavage stages, declining in prevalence as gestation progresses. A mouse model of mosaicism revealed that aneuploid cells are progressively depleted from the embryo, consistent with a "clonal depletion" hypothesis, and mosaic euploid-aneuploid embryos have comparable developmental potential to normal embryos, provided they contain a sufficient proportion of euploid cells. A recent observational study showed that mosaic embryos can develop into euploid newborns. Of 18 patients undergoing the transfer of a mosaic embryo, 6 achieved clinical pregnancy and delivered a healthy singleton infant at term^41. However, the mosaic embryos are usually regarded as abnormal and transfer of mosaic embryos are not recommended in present clinic. Given the limited data about the safety of transferring mosaic embryos, we plan to freeze all mosaic embryos in this study until the risk benefit ratio is clearer.

### 3 STUDY DESIGN

This is a multicenter, randomized clinical trial comparing the efficacy and safety with transfer of embryos selected by next generation sequencing (NGS) and morphologic criteria versus by morphological criteria alone. Subjects with a good prognosis for IVF success who obtain 3 or more good-quality blastocysts on day 5 of embryo culture will be randomized to the PGS or the non-PGS group. A freeze-all strategy and frozen single blastocyst transfer will be performed in both the PGS and the non-PGS groups. Subjects in the PGS group will have 3 blastocysts sequenced and euploid embryos will be subsequently transferred one by one by FET. Subjects in the IVF group will have three day 5 blastocysts selected for the first 3 transfers based on morphology assessment. The cumulative live birth rate will be counted after transfers of all euploid embryos in the PGS group and 3 blastocysts in the IVF group (up to 3 transfers of single blastocysts in both groups) within 1 year after randomization in both groups.

### 4 SELECTION AND ENROLLMENT OF SUBJECTS

#### 4.1 Inclusion Criteria

4.1.1 Women who are participating in their first cycle of IVF or ICSI

4.1.2 Women ages 20 to 37 years.

4.1.3 Women who obtain 3 or more good-quality blastocysts defined as morphological score of inner cell mass B or A, trophectoderm C or better, and grade 4 or better on day 5 of embryo culture will be randomized.

## 4.2 Exclusion Criteria

4.2.1 Women with a uterine cavity abnormality, such as a uterine congenital malformation (uterus unicornate, bicornate, or duplex); untreated uterine septum, adenomyosis, submucous myoma, or endometrial polyp(s); or with history of intrauterine adhesions.

4.2.2 Women who are indicated and planned to undergo PGD, for example, abnormal parental karyotype, diagnosed with monogenic disease, or at high risk for transmitting a genetic disease;

4.2.3 Women who use donated oocytes or sperm to achieve pregnancy;

4.2.4 Women with contraindication for assisted reproductive technology or for pregnancy, such as poorly controlled Type I or Type II diabetes; undiagnosed liver disease or dysfunction (based on serum liver enzyme testing); renal disease or abnormal serum renal function; significant anemia; history of deep venous thrombosis, pulmonary embolus, or cerebrovascular accident; uncontrolled hypertension, known symptomatic heart disease; history of or suspected cervical carcinoma, endometrial carcinoma, or breast carcinoma; undiagnosed vaginal bleeding.

## 4.3 Study Enrollment Procedures

4.3.1 Recruitment: Potential subjects who meet the preliminary screening criteria (age 20 to 37 years and undergoing their first cycle of IVF) after opting for IVF will be referred to the local investigator before the start of ovarian stimulation by other physicians at study sites. A copy of the informed consent will be given to the interested subjects to read before meeting with local investigators.

4.3.2 Screening log: A standard screening log will be kept by local investigators in each study site to record all the subjects screened (subjects committing to IVF and offered the study), reasons for ineligibility and for nonparticipation of eligible subjects. The local screening log will be reported to DCC monthly.

4.3.3 Consent procedure: The local investigator will explain this trial in detail to potential subjects and their partners and answer any questions raised by them prior to signing the written informed consent to participate in the study. At the start of ovarian stimulation, written consent will be obtained from both the female subject and her partner. A copy of the signed written informed consent form will be given to the subjects.

4.3.4 Assignment: On day 5 of embryo culture, eligible subjects will be randomized via an online central randomization system. The assignment will be informed to subjects and their physicians.

## 5 STUDY INTERVENTIONS

### 5.1 Interventions, Administration, and Duration

The study intervention is PGS for embryo selection as compared with conventional morphologic score alone.

Subjects in the PGS group will have 3 blastocysts biopsied on Day 5 and sequenced, which will be selected by morphology score, i.e. the best embryos by morphology will be selected for PGS. Euploids will be transferred one by one by eSET. The selection of embryos for PGS as well as the transfer order of euploid embryos will be decided by morphology score, i.e. the best embryos by morphology will be chosen. The other embryos will be frozen according to local routine.

Subjects in the non-PGS group will have 3 day-5 blastocysts selected according to morphologic score for the first 3 transfers. The order of transfer will be determined by morphologic score, i.e. the best embryo will be transferred first. A single frozen blastocyst will be transferred each time. The priority of transfer will be determined by morphology score.

In both groups, if there is a tie between embryos in morphology score on day 5, the day 3 embryo score will be used to select the embryo for PGS and/or transfer.

#### 5.1.1 Blastocyst morphologic score criteria: Gardner criteria 

Blastocysts will be graded on a 1 to 6 scale determined by degree of expansion and hatching status, as follows:

Grade 1 (early blastocyst): blastocoele < 1/2 of total embryo volume;

Grade 2 (intermediate blastocyst): blastocoele  $\geq$  1/2 of total embryo volume;

Grade 3 (full blastocyst): blastocoele fully occupies the embryo;

Grade 4 (expanded blastocyst): blastocoele is larger than early blastocyst and zona pellucida (ZP) demonstrates thinning;

Grade 5 (hatching blastocyst): herniation of trophectoderm cells from the ZP;

Grade 6 (hatched blastocyst): blastocyst has escaped the ZP.

For blastocysts at Grades 3 to 6, the inner cell mass (ICM) and trophectoderm (TE) will also be graded.

The ICM is graded as follows:

A (many ICM cells packed together tightly); B (several ICM cells grouped loosely) and C (very few ICM cells).

TE was graded as follows: A (many TE cells forming multiple epithelial layers); B (few TE cells consisting of a loose epithelium) and C (very few large TE cells).

The pictures of blastocyst grading are found in Figure 2 :

[figure not shown]

**Fig.2 Examples of blastocyst grading: (a)3AA blastocyst; (b) 3AB blastocyst; (c) 3BC blastocyst; (d) 4AB blastocyst; (e) 4BB blastocyst; (f) 4BC blastocyst; (g) 5AA blastocyst; (h) 5AB blastocyst; (i) 5BC blastocyst; (j) 6AA blastocyst; (k) 6AB blastocyst; (l) 6BC blastocyst. Bars=50 µm.**

### 5.1.2 Blastocyst biopsy:

03/07/2017

- 1) Procedure: For blastocysts with score 4BC or better on Day 5 of embryo culture, trophectoderm biopsy will be performed with laser method.
  - a) Before the operation, biopsy dishes, polymerase chain reaction (PCR) tubes and fixation slides will be prepared and labeled with patient's name, medical record number and embryo number. A very small channel (10-20  $\mu\text{m}$ ) will be opened at the site opposite to the ICM on the zona pellucida of each blastocyst with a diode laser. By entering the zona with the micropipette, 3–5 herniating TE cells will be aspirated with moderate suction, and detached from the blastocyst by synchronously firing several laser pulses at the area of constriction. Next, the aggregate of TE cells will be placed intact into a PCR tube after several washes through hypotonic solution. After the operation, physiological status of the embryo should be observed and recorded.
  - b) This operation should be completed by the same embryologist at each study site with more than 3-years experience. Different micromanipulators and different laser frequency used in the participating IVF centers are allowed.
- 2) Potential side effects: Mechanical damage of embryos, possible impairment of development and implantation potential. It has been reported that mechanical or chemical manipulation of the zona pellucida can increase the risk of monozygotic twinning.

#### 5.1.3 NGS tests:

Different NGS platforms (*Illumina MiSeq/HiSeq*, *Life Tech PGM/Proton*) applied in different IVF centers are allowed. The operation procedures will follow the instruction by manufacturers (*Illumina or Life Technologies*).

- 1) Procedure:
  - a) Whole genome amplification (WGA): Blastocysts will be firstly lysed and genomic DNA will be amplified with the routine amplification methods at different sites. Common methods include the Sureplex (Rubicon), multiple displacement amplification (MDA) using Repli-G Midi (Qiagen), and MALBAC (Yikon Genomics). Reagent-positive control (genomic DNA) and negative control (amplification mixture only) are necessary for WGA.
  - b) Library preparation: WGA products will be purified and quantified, and subsequently fragmented into a library of small fragments (100 to 200 bp). DNA fragmentation by adding unique adapter sequences will be further performed to simultaneously analyze different blastocyst samples.
  - c) Sequencing and sequence analysis: The libraries will be sequenced with paired-end dual indexing using different NGS platforms (*Illumina MiSeq/NextSeq550 or Life Tech PGM/Proton*). Reads will be aligned to the human genome hg19 and then filtered by removing unmapped reads, duplicate reads and reads with low mapping scores. The following bioinformatics will be accomplished by corresponding software according to the different platforms. Each chromosome will be divided into intervals each approximately

03/07/2017

covering 1 Mb of sequence. Filtered reads from each sample will be then mapped into the corresponding chromosome interval or bin. The count data in each bin will be normalized using GC content, and in-silico reference data in order to remove bias. The normalized bin counts will be then re-expressed as copy number by assuming the median autosomal read count corresponds to copy number two. The bin-wise copy number values for each chromosome will be smoothed with a 13-bin sliding median. Automated copy-number status for each chromosome will be determined using the median of smoothed copy-number values across the chromosome as described elsewhere.

- d) Classification of results: Chromosomal aneuploidies are detected as copy number imbalances. In particular, the analysis pipeline expects a default copy number of 2 for autosomes; the sample sex and sex chromosome copy numbers are determined by an initial calling algorithm. Embryos will be diagnosed as abnormal or aneuploid if the median chromosomal copy number measures deviated from the default copy number. Chromosomal gain or trisomy (copy number >2) and chromosomal loss or monosomy (copy number <2) are seen as horizontal green bars above and below, respectively, the copy number state of 2. Embryos will be diagnosed as normal or euploid if the generated plot showed no gain or loss.

If amplification failure occurs, the embryo will be regarded as an unknown result and transferred according to the same morphologic grading as the IVF group and analyzed by ITT in the assigned treatment group.

Mosaic embryos will be frozen and not transferred in this study, until we have further evidence of the safety and efficacy of transferring mosaic embryos. Because the interpretation of an acceptable embryo to transfer is an evolving field, we will modify our policies regarding transferable embryos as new information appears.

- 2) Potential side effects: Possible existence of false positives and false negatives due to contamination or mosaicism leads to transfer of abnormal embryos or discarding of viable ones. The result is defined as false negative when the actual chromosomal constitution is abnormal or chaotic but the sequencing result is euploid. The result is defined as false positive when the actual chromosomal constitution is euploid but the sequencing result is abnormal or chaotic.

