### Design and Outcomes

This is a multicenter, randomized trial comparing the efficacy and safety of transfer of single embryo at the blastocyst stage selected by next generation sequencing (NGS) versus conventional morphological criteria. Subjects with 3 or more blastocysts on day 5 of embryo culture will be randomized to the PGS or IVF group. A Freeze-all strategy and a single frozen blastocyst transfer will be performed in both the PGS and IVF groups until all study-specific embryos have been transferred. Subjects in the PGS group will have 3 blastocysts sequenced and euploid embryos will be subsequently transferred one by one. Subjects in the IVF group will have all of their embryos which have reached the blastocyst stage vitrified on day 5 or 6. The cumulative live birth rate will be counted after transfers of all euploid embryos in the PGS group and up to 3 blastocysts in the IVF group within 1 year after randomization in both groups if the study-specific embryo transfers are not finished.

03/07/2017

The primary outcome is cumulative live birth rate over the (up to) 3 embryo transfers. The secondary outcomes include the Good Birth Outcome rate, cumulative pregnancy rate, cumulative pregnancy loss rate, multiple pregnancy rate, duration of pregnancy, birth weight, cumulative incidence of maternal and neonatal complications (including fetal anomalies) and number of transfers to achieve live birth. The tertiary outcomes are the rates of pregnancy, pregnancy loss and live birth after initial transfer between PGS and IVF.

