### **Interventions and Duration**

1. Ovarian hyperstimulation (10 to 30 days): All subjects will receive controlled ovarian hyperstimulation with gonadotropin releasing hormone (GnRH) agonist long or short protocol or GnRH antagonist protocol as per physician preference.
2. Oocyte retrieval, ICSI and embryo culture (5 days): Oocyte retrieval will be performed 34 to 36 hours after oocyte maturation trigger by hCG, GnRHa, or dual trigger. Intracytoplasmic sperm injection (ICSI) will be applied for all included subjects. On the day 5 of embryo culture, women with 3 or more blastocysts will be randomized in a 1:1 ratio into one of two groups: the PGS or the non-PGS group.
3. Embryo biopsy, vitrification and NGS test: Subjects in both groups will have all their embryos frozen and undergo single frozen blastocyst transfer. Subjects assigned to the PGS group will have 3 blastocysts biopsied on day 5 and tested by NGS. Subjects assigned to the non-PGS group will have 3 day-5 blastocysts selected for the first 3 transfers. In both groups, the best blastocysts by morphologic criteria will be selected for NGS or transfer. Assisted hatching will not be performed.
4. A recovery period after ovarian stimulation of 6-10 weeks to allow, shedding of the endometrial lining, decline of steroid hormones, and restoration of normal ovarian function: Endometrial preparation will be started at the second or third menses cycle after oocyte retrieval. Both natural ovulation cycle and artificial regimen will be allowed for endometrial preparation.
5. Pregnancy evaluation and follow-up (2 weeks to 10 months): All pregnancies will be followed up till termination or delivery.
6. Outcome of subsequent transfers (12-21 months): If live birth isn't achieved by the initial transfer and there are euploid embryos in the PGS group or morphologically transferrable embryos in the IVF group, subsequent single embryo transfer(s) will be performed (up to 3 or up to one year after randomization). The cumulative live birth rate will be counted after transfers of all euploids in the PGS group and 3 blastocysts in the IVF group or all transfers within 1 year after randomization in both groups.

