### 5.3 Concomitant Interventions

#### 5.3.1 Required Interventions

Participants will receive controlled ovarian hyperstimulation (COH) with agonist via a long or short protocol, or an antagonist protocol, HCG or GnRH $\alpha$  trigger final oocyte maturation, and standard ultrasound guided oocyte retrieval, ICSI procedure and embryo culture according to clinical routine in different study sites. An elective freeze-all strategy and single frozen embryo transfers will be employed. The transfer order in the PGS group will be decided by both NGS results and embryo morphologic score, while transfer order in the non-PGS group will be decided by morphologic score alone. The endometrium for FET will be prepared either through a natural ovulation cycle or artificial cycle. The choice of which will be up to the site investigator. Luteal phase support will be administrated according to the routine in different sites. A pregnancy test will be performed 2 weeks after embryo transfer. If pregnancy is confirmed, luteal phase support will be continued till 10 weeks of gestation. The follow-up will continue until termination or delivery.

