### 6.2.3 Intervention Discontinuation Evaluations

After randomization, further participation in the study will be discontinued in the following situations: a) no euploid embryo is obtained in patients assigned to the PGS group after NGS test; b) Subjects who run out of the protocol-specified embryos; c) Subjects who do not complete transfers of the protocol-specified embryos within 1 year after randomization. Subjects who conceive will be followed to the termination of the pregnancy.

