## 9.2 Outcomes

### 9.2.1 Primary outcome

The primary outcome is the cumulative live birth rate over the (up to) 3 embryo transfers. Live birth is defined as the delivery of any viable infant at 28 weeks or more of gestation after our interventions, and cumulative live birth rate is calculated by dividing the number of women achieving live birth after transfers of all euploid embryos in the PGS group or 3 blastocysts in the IVF group within 1 year after randomization, by the total number of women randomized to the specific group.

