#### 9.5 Data Analyses

The primary analysis will be performed in accordance with the principle of intent-to-treat. Continuous variables will be described as mean  $\pm$  standard deviation for the normally distributed variables and as median and range for the non-normally distributed variables. Category variables will be presented as frequency and percentage. The differences in the cumulative live birth rate in the two treatment arms will be compared by absolute risk difference and its 95% confidence interval (CI). The relative risk and its 95% CI will also be calculated. Non-superiority of PGS to IVF will be considered to be established if the upper limit of the 95% CI of absolute risk difference was shown to lie below the non-superiority margin of 7%.

The differences in the secondary outcomes such as rate of Good Birth Outcome, cumulative pregnancy rate, cumulative pregnancy loss rate, multiple pregnancy rate obstetric and neonatal complications will be tested by Person chi-square analyses. The absolute difference and 95%CI as well as relative risk and 95% CI will also be calculated. The difference between duration of pregnancy, birth weight and times of embryo transfer will be tested by student t test and non-parameter test if necessary.

The tertiary outcomes such as the rates of pregnancy, pregnancy loss and live birth after the first transfer will be analyzed with Pearson chi-square test. Cost-effectiveness analysis will be done by decision analytic model with TreeAge Pro 2014 (2014 Version; TreeAge

software). Cost effectiveness is defined as an incremental cost effectiveness ratio (ICER). The ICER for live birth was calculated as the difference in cost between two treatment groups divided by the difference in live birth rates between the two groups. The secondary analysis will be performed according to per-protocol analyses. The primary and secondary outcomes will be compared according to actual treatment that subjects received and among subjects who complete embryo transfer(s).

Subgroup analyses will be performed according to different stimulation protocol (e.g. agonist long, agonist short, and antagonist protocol), different endometrial preparation protocol for FET (e.g. natural ovulation cycle and artificial cycle), age groups (e.g. 20~30 group, 30~35 group and >35 group), with or without history of recurrent spontaneous abortion.

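### The stop rule in section 6.2.3(a) ends participation for PGS women who have no euploid embryo but still hold a no-result embryo that section 5.1.3 makes transferable

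*Combined protocol and SAP*

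**What the plan says.** Section 5.1.3(d) covers amplification failure in the PGS arm. Such an embryo counts as "an unknown result and transferred according to the same morphologic grading as the IVF group and analyzed by ITT in the assigned treatment group". The same paragraph calls an embryo euploid only if a plot was generated and showed no gain or loss, so an embryo without a result is not euploid.

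Section 6.2.3 lists three situations that end participation after randomization. Item (a) is that "no euploid embryo is obtained in patients assigned to the PGS group after NGS test". Item (b) is running out of protocol-specified embryos, and item (c) is not finishing the transfers within one year.

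Other passages bear on which rule was meant:

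- Synopsis, Interventions and Duration, item 6: further transfers follow a failed one if "there are euploid embryos in the PGS group or morphologically transferrable embryos in the IVF group". No-result embryos are not mentioned.
- Synopsis, Design and Outcomes: single frozen transfers continue in both groups "until all study-specific embryos have been transferred".
- Section 9.2.1: "The primary outcome is the cumulative live birth rate over the (up to) 3 embryo transfers". Its calculation sentence counts women with a live birth "after transfers of all euploid embryos in the PGS group or 3 blastocysts in the IVF group within 1 year after randomization" and divides by all women randomized to the group.
- Section 9.5: "The primary analysis will be performed in accordance with the principle of intent-to-treat".

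**The concern.** Take a PGS woman whose three biopsied blastocysts give two aneuploid results and one amplification failure. Section 5.1.3 says the third embryo is transferred. Section 6.2.3(a) says her participation ends. No passage states which rule prevails.

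The error runs in one direction. If she is stopped, she remains in the denominator and contributes no live birth. An IVF woman stops only when her study embryos or the year run out. Compared with section 5.1.3, following 6.2.3(a) can therefore only remove live births from the PGS arm. The trial claims non-superiority when the upper confidence limit for PGS minus IVF lies below 7 points, so a lower PGS rate makes the claim easier to reach.

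Biopsy and sequencing are done locally at eight planned centres with different amplification methods and platforms (Synopsis, Sample Size and Population; sections 5.1.3 and 5.2). Both the frequency of no-results and the reading of the two rules could therefore differ by site.

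**Working it through.** **The plan's own figure.** With 65% in each group, a 7-point margin, one-sided 5% and 80% power: n = (1.645 + 0.842)² × 2 × 0.65 × 0.35 / 0.07² ≈ 574.1 (unrounded normal quantiles), rounded up to 575 per group. 575 × 1.05 = 603.75, so 604 per group and 1208 in total, as stated. The point here does not change the sample size.

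**Inputs from the documents.** Three embryos are tested per PGS woman (5.1). Euploidy is about 60% (2.1). Alternative euploidy figures are 64% to 66%, from the aneuploidy rates of 36.1% (under 38 years, blastocyst biopsies) and 33.99% (ages 30 to 38) in section 2.2, and 40% to 56% for top-scoring blastocysts in the rationale for morphologic scoring. Section 2.2 also reports 44.9% aneuploidy under 35 years, which is 55.1% euploid and so falls inside that last range.

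**Assumptions not in the documents.** The no-result share per embryo is f = 1% to 5%. The live-birth chance per no-result transfer is q = 14.8% to 29.5%. The upper value is 1 − 0.35^(1/3) = 0.295, the per-transfer rate that gives 65% over three transfers. The lower value is half of that. Embryos are taken as independent, and every site is taken to follow 6.2.3(a).

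**Formulas.** Let g be the euploid share among embryos with a result, and a = (1 − g)(1 − f) the chance that an embryo has a result and is not euploid.

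- Women with no euploid and at least one no-result embryo: (f + a)³ − a³.
- Fall in the PGS rate if they are stopped: (f + a)³ − (f(1 − q) + a)³. Transfer order does not matter, because these women have no euploid embryo.

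**At g = 0.60:**

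| f | q | a | Women affected | Of 575 | Fall in PGS rate |
|---|---|---|---|---|---|
| 0.01 | 0.148 | 0.396 | 0.406³ − 0.396³ = 0.48% | 2.8 | 0.406³ − 0.40452³ = 0.07 points |
| 0.02 | 0.295 | 0.392 | 0.412³ − 0.392³ = 0.97% | 5.6 | 0.412³ − 0.4061³ = 0.30 points |
| 0.05 | 0.148 | 0.380 | 0.430³ − 0.380³ = 2.46% | 14.2 | 0.430³ − 0.4226³ = 0.40 points |
| 0.05 | 0.295 | 0.380 | same | 14.2 | 0.430³ − 0.41525³ = 0.79 points |

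In births per 575 women the range is 575 × 0.00073 ≈ 0.4 to 575 × 0.0079 ≈ 4.5.

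**Sensitivity to euploidy:**

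- g = 0.66, f = 0.01, q = 0.148: 0.05 points. g = 0.639, f = 0.05, q = 0.295: 0.66 points. So the range is 0.05 to 0.66 at the section 2.2 figures.
- g = 0.56, f = 0.05, q = 0.295: 16.9 women, 0.94 points.
- g = 0.40, f = 0.05, q = 0.295: 30.6 women, 1.66 points.

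**The case against.** The best reply is that the documents largely settle the matter. Section 5.1.3 is the only place that deals with amplification failure, and it gives a definite instruction. Section 6.2.3 stands among the evaluations. Section 8, which sets criteria for discontinuing the intervention, names only patient or physician request and has no stop for lack of a euploid embryo. Item (a) could be shorthand for testing that leaves nothing to transfer, and a woman with a no-result study embryo has not run out of embryos under item (b).

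Most of this stands. Section 5.1.3 is the rule the authors meant, and a careful site would probably follow it. But item (b) already covers exhaustion of embryos, so (a) is a separate trigger. It names the PGS group, the NGS test and the condition, and Section 8 does not override it. Staff who work from 6.2.3 would stop the woman.

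It is also true that the size depends on assumed rates, that the upper figures need the highest no-result rate, the highest live-birth chance and every site stopping, and that euploidy above 60% shrinks the effect. If only some of the affected women were stopped, it would be smaller again.

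A reader might infer more: that section 9.2.1 excludes births from no-result embryos from the primary numerator. The documents do not support this. The calculation sentence does name only euploid transfers, but the lead sentence speaks of up to three transfers without that limit, and the intent-to-treat rules in 5.1.3 and 9.5 favour counting these births. Section 9.2.1 needs clearer wording; it is not a second error.

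**Conclusion.** Section 6.2.3(a) is wrong as written. Two stated rules conflict for a small, definable group, and the one that stops treatment is not the intended one. The conflict bears on the primary numerator, and its direction favours the non-superiority claim.

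The size is small: 0.07 to 0.79 points at the protocol's 60% euploidy, 0.05 to 0.66 at 64% to 66%, and an upper end of 0.9 to 1.7 at 56% down to 40%, all against a 7-point margin. These figures assume a 1% to 5% no-result share, 14.8% to 29.5% live birth per no-result transfer, independent embryos, and all sites following 6.2.3(a).

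It does not follow that the trial's result was materially biased. The documents give no no-result rate and do not show that any site stopped such a woman. The point is a correction of wording and does not challenge the design.

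**What to change.** In section 6.2.3(a), make the trigger *no euploid and no unknown-result embryo is obtained*. That clause alone removes the conflict.

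For consistency, write *euploid or unknown-result study embryos* for the PGS group wherever the text names only euploid embryos: Synopsis (Design and Outcomes; Interventions and Duration, item 6), section 3, section 5.1, section 5.3.1 (pregnancy evaluation and follow-up) and section 9.2.1. It is then explicit that every live birth within the window from an embryo that section 5.1.3 makes transferable counts in the primary numerator. A euploid-only count could be added as a sensitivity analysis.

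The cost is wording only. No extra patients, visits or data are needed, because section 6.2.2 already records the NGS result for the three blastocysts. The sample size is unchanged. The PGS rate will include a few untested embryos, which section 5.1.3 already intends.
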